## 4. Conclusion

Globally, the prevalence of AR is still rising, and the recurrence rate is still high, while the standard pharmacotherapy of AR fails to focus on reducing recurrences, making it urgent to find new therapies to solve this problem. Thus, this study may provide evidence for the efficacy of pharmacotherapy of AR recurrence by TCM and provide more options for the treatment of AR in clinics.

### 4.1. Trial Status

The recruitment started on September 1, 2021, and is expected to finish on December 31, 2022, 16 months in total.

## Figures and Tables

**Figure 1 fig1:**
[figure not shown]
Study flowchart.

**Table 1 tab1:** Syndrome differentiation criteria of QDBS.

	Qi deficiency	Blood stasis
Primary symptoms	Shortness of breath; mental fatigue; and feeble pulse	Obstruction of collaterals manifestations (purplish lips, gingiva, and nails); purplish tongue or tongue with ecchymosis; varicose veins under the tongue; and unsmooth pulse/deep and wiry pulse/slow and wiry pulse.

Secondary symptoms	Spontaneous sweating; unwillingness to speak; and pale tongue	Scaly skin; hypoesthesia; depressive; amnesia; and paresthesia.

*Note*. Diagnosis of each syndrome element should include two primary symptoms or one primary symptom and two secondary symptoms, simultaneously. The diagnosis of QDBS requires meeting both diagnoses of “Qi deficiency” and “blood stasis,” simultaneously.

**Table 2 tab2:** Study inclusion and exclusion criteria.

Inclusion criteria	• Patients who meet the above diagnostic standards
	• Patients with a positive skin prick test (SPT) of HDM of grade 2 or above
	• Patients between 18 and 65 years regardless of gender
	• Patients who have not received any medication for AR in the past two weeks
	• Patients who agree to participate in this study and sign the informed consent form (S3)

Exclusion criteria	• Patients combined with severe nasal septal deviation, chronic nasal-sinusitis, bronchial asthma, nasal polyps, and other diseases
	• Patients with heart, liver, and kidney disorders or autoimmune diseases
	• Patients with mental illnesses, mental disorders, and/or unable to cooperate well enough to complete the study
	• Patients during pregnancy, lactation, or pregnancy preparation
	• Patients who are allergic to the composition of the trial drugs
	• Patients who have received glucocorticoids, leukotriene receptor blockers, antihistamines, or anti-inflammatory drugs within the past two weeks
	• Patients with skin pathological changes at the site of the skin prick test
	• Patients who have previously participated in specific immunotherapy
	• Patients who have participated in other clinical studies in the past two months. Patients with any one of the above shall be excluded.

**Table 3 tab3:** Participants' timeline of this study.

[figure not shown]

*Note*. w, week; w1, the first week; w2, the second week; Wx, timepoint when subjects meet the clinical control standard; drug withdrawal (wx+2), timepoint when subjects meet the clinical control standard and last for two weeks.

**Table 4 tab4:** Ethical review approvals.

Number	Ethics committees' name	Approval registration number
1	Medical Ethics Committee of the Hospital of Chengdu University of Traditional Chinese Medicine	2021KL-046
2	Ethics Committee on Biomedical Research, West China Hospital of Sichuan University	n/a
3	Medical Ethics Committee of the Sichuan Provincial Hospital of Integrated Traditional Chinese and Western Medicine	KY-HX-2021-039

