## 1. Introduction

Allergic rhinitis (AR) is one of the most common allergic diseases worldwide and it is a global health problem affecting 40% of the world's population [1]. The prevalence of AR has been increasing worldwide since the 1960s [2] and has dramatically increased in recent years [3]. For example, AR showed a sharp increase in prevalence from 11.1% to 17.6% over 6 years in major Chinese cities [4]. The repeated attacks of AR are one of the main difficulties faced by patients. A study of 7-year-olds in South Korea found that the two-year recurrence rate for AR is 72% [5].

The pharmacotherapy of AR includes corticosteroids, antihistamines, and decongestants, most of which focus on suppressing immune factors and controlling immediate symptoms. Even though pharmacotherapy has proven to be highly effective in controlling allergic symptoms, most of the pharmacological management approaches recommended in the guidelines for AR have not been evaluated for efficacy in controlling recurrences. Furthermore, their long-term use can cause side effects, including epistaxis, mucosal dryness, and other adverse reactions, reducing patient compliance. Globally, while the standard pharmacotherapy of AR is relatively mature, the prevalence of AR is still rising [6, 7], and the recurrence rate is still high [8], making it urgent to find new therapies to solve this problem.

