### 2.6. Sample Size

In this study, the 6-month recurrence rate was used as the basis for sample size estimation. Combined with our previous research and the literature, the six-month recurrence rates of AR treated with MYN and mometasone furoate aqueous nasal spray were approximately 50% and 75% [27], respectively. Using 5% as the superiority margin, an acceptable alpha of 2.5% (one-tailed), and an acceptable beta of 20%, 86 participants were required in each group. To allow for a 10% loss to follow-up, we will recruit 190 subjects in total.

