#### 2.9.2. Control Group

Mometasone furoate aqueous nasal spray (NASONEX) is produced and packed by Schering-Plow Labo N. V. (drug batch number: H20140100). Mometasone furoate aqueous nasal spray will be administered intranasally, and two pumps/nostril will be sprayed once a day. The drug will not be administered once the patient meets the clinical control standard for two weeks. The shortest treatment time will be not less than four weeks, and the longest treatment time will be not more than three months.

Any other Western or Chinese medicines for AR are prohibited during this trial.

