#### 2.10.2. Primary Outcomes

The primary outcome is the six-month recurrence rate of AR after intervention withdrawalFollow-up: subjects will enter the follow-up period after withdrawal of medications. Once a relapse occurs, the patient's recurrence time will be recorded, and the follow-up ends. Otherwise, the follow-up will continue until six months after drug withdrawal.Definition of recurrence/relapse: when the RCAT score ≤21 during follow-up, the patient will be considered in a relapse stateDefinition of six-month recurrence rate: six-month recurrence rate = number of recurrent AR patients in six months/total number of patients × 100%The RCAT has sufficient reliability, validity, and responsiveness and is a simple patient self-assessment scale [29]. RCAT can be used to assess a patient's rhinitis control status in clinical practice [30]. During the treatment stage, we will collect the RCAT scale online once a week, and during the follow-up stage, we will collect the RCAT scale online every two weeks.

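### Relapse is defined by the RCAT score alone, so a patient kept above 21 in follow-up by an AR medicine or another suppressive drug counts as recurrence-free

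*Protocol article*

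**What the plan says.** **Outcome (Section 2.10.2).** A patient is in relapse when the RCAT is 21 or lower in follow-up; no medication component is given. The primary outcome is "six-month recurrence rate = number of recurrent AR patients in six months/total number of patients × 100" per cent. On timing, "during the follow-up stage, we will collect the RCAT scale online every two weeks". Follow-up ends at relapse. "Otherwise, the follow-up will continue until six months after drug withdrawal".

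**On-study drug rule (Section 2.9.2).** "Any other Western or Chinese medicines for AR are prohibited during this trial". This is the only on-study drug restriction in the article, and it gives no consequence for the outcome.

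**Entry rules (Table 2).** There are two separate criteria. One goes by indication: "Patients who have not received any medication for AR in the past two weeks". The other excludes by drug class: "Patients who have received glucocorticoids, leukotriene receptor blockers, antihistamines, or anti-inflammatory drugs within the past two weeks".

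**Setting.** Patients are not blinded (Section 2.8) and rate the RCAT themselves (Section 2.10.2). The Limitations paragraph of the Discussion accepts that the open-label design may bias the evaluation of relapse control.

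**The concern.** The outcome is meant to show whether the disease stays controlled after the study drug is withdrawn. A score above 21 shows that only if nothing else is holding it up. The definition does not ask. A patient whose symptoms return and who treats them successfully before the next score has relapsed in the clinical sense, yet enters the primary outcome as a success. A patient on an antihistamine or a systemic steroid for an unrelated condition may have a relapse masked in the same way.

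If this happens equally in both arms, the difference shrinks. If it differs by arm, which is possible when patients know their treatment, the difference is biased in a direction that cannot be known beforehand. The one-month recurrence rate and the time to relapse are exposed too, because even a delay in detection changes them.

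**Working it through.** **1. How the stated rules score each case in follow-up**

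| Case | Section 2.9.2 | Section 2.10.2 |
|---|---|---|
| No other drug, RCAT 21 or less | not relevant | recurrence |
| AR medicine taken, RCAT above 21 | prohibited | no recurrence |
| Table 2 class drug for another condition, RCAT above 21 | not clearly covered | no recurrence |

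The second row needs no special reading of the drug rule. The ban applies, it is broken, and the outcome is still a success.

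**2. Delay or loss**

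Six months is about 26 weeks, so there are about 26/2 = 13 scores. A short course affects one or two of them, and a later score can still record the relapse. A relapse is lost to the six-month rate only if use is sustained, if it falls near month 6, or if the episode is over before the next score.

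**3. The plan's own figure**

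Inputs from Section 2.6: recurrence 75% (mometasone) and 50% (MYN), margin 5 points, one-sided alpha 2.5%, power 80%.

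n per arm = [0.75×0.25 + 0.50×0.50] × (1.960 + 0.842)² / (0.25 − 0.05)² = 85.85, so 86. The stated 86 is reproduced and is not in dispute.

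**4. Illustration of size**

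The documents give no rate of such drug use, so the share h of relapses lost for good is an assumption.

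Observed rate = true rate × (1 − h). Power with the margin = Φ[(difference − 0.05)/SE − 1.960], where SE = √{[p₁(1−p₁) + p₂(1−p₂)]/86}. The last column uses no margin (standard two-proportion formula, pooled variance under the null), because the tests in Section 2.12 mention none.

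| h, equal in both arms | Observed rates | Difference (points) | Power, 5-point margin | Power, no margin |
|---|---|---|---|---|
| 0% | 75% v 50% | 25 | 80% | 93% |
| 2% | 73.5% v 49% | 24.5 | 77% | 92% |
| 5% | 71.25% v 47.5% | 23.75 | 73% | 89% |
| 10% | 67.5% v 45% | 22.5 | 66% | 85% |
| 20% | 60% v 40% | 20 | 52% | 75% |

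Unequal loss, 86 per arm:

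- Mometasone arm only: 5% gives 71.25% v 50%, 21.25 points, power 61% with the margin; 10% gives 67.5% v 50%, 17.5 points, power 39%.
- MYN arm only: 5% gives 75% v 47.5%, 27.5 points; 10% gives 75% v 45%, 30 points.
- MYN arm only, when both true rates are 75%: the chance of a result favouring MYN in a test without margin, nominally 2.5%, is 8.0% at 5% lost and 19% at 10% lost. With the 5-point margin it is 1.6% and 5.5%.

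These figures treat every masked relapse as lost. By step 2, the share lost should be smaller than the share of relapses masked at some score.

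**The case against.** **The article condenses a fuller protocol.** Section 2.17 says the complete protocol is on the registry website. A list of prohibited drugs and the recording of concomitant medication may well be there, and their absence here is no finding. This stands. But the article states the relapse definition in full, and as stated it scores a treated patient above 21 as a success. A list of prohibited drugs would not change that.

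**Table 2 and Section 2.9.2 do not contradict each other.** A reader might infer that the class exclusion at entry should carry through follow-up. The documents do not support this. An entry washout and an on-study ban can have different jobs, and the article gives no reason for the washout. It might, for example, protect the skin prick test, which entry requires.

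**The on-study ban may already cover most of these drugs.** A reader might infer that antihistamines and steroids for other conditions are allowed on study. The Introduction says "The pharmacotherapy of AR includes corticosteroids, antihistamines, and decongestants", so a site could treat those classes as banned outright. Table 2 does list medication for AR and the drug classes as separate criteria, which points the other way, and general anti-inflammatory drugs remain unclear. Neither reading is certain, and under either one use has no effect on the outcome.

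**The effect is likely to be small.** Asthma, nasal polyps, chronic sinusitis and autoimmune disease are excluded, and short courses mostly delay detection. Advice at recurrence, payment per visit and a compliance index (Section 2.13) may encourage reporting. This stands and limits the claim.

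**Conclusion.** The point holds as a fault in the outcome rule: relapse depends on RCAT alone, and the on-study ban has no stated consequence for the outcome. Its size is unknown and probably modest. The figures above show the direction and how sensitive the trial would be; they are not estimates, since every lost share is assumed. Loss of 2% to 10% in both arms would cost 0.5 to 2.5 points of the assumed 25. Unequal loss could move the result either way, and the open-label design makes that possible without showing that it will occur. The finding does not rest on a conflict between Table 2 and Section 2.9.2, and the sample size is unaffected.

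**What to change.** 1. Amend Section 2.10.2 so that starting any AR medicine during follow-up counts as recurrence at its start date. The one-month rate and the time-to-event analyses should use the same rule.
2. Add one question to the existing online RCAT: use of any Table 2 drug class since the last score, with date and reason. Wording it to include any other medicine taken for rhinitis lets the same item supply rule 1.
3. Keep patients who need such a drug for another indication in the primary analysis by their RCAT scores, and add one sensitivity analysis that counts this use as recurrence.

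Do not ban the classes regardless of indication. With up to three months of treatment and six of follow-up, that could deny patients treatment for unrelated conditions for about nine months.

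The cost is a wording amendment, one form item and one added analysis. Recurrence may come out slightly higher in each arm.

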## Data Availability

Data sharing is not applicable to this article as no datasets were generated or analyzed during the current study. The data will be shared after the trial is finished.

## Abbreviations

AR: Allergic rhinitis
TCM: Traditional Chinese medicine
YPF: Yupingfeng powder
MYN: Modified Yupingfeng nasal spray
QDBS: Qi deficiency and blood stasis syndrome
RCAT: Rhinitis control assessment test
VAS: Visual analog scale
RQLQ: Rhinoconjunctivitis quality of life questionnaire
TNSS: Total nasal symptom score
TOSS: Total ocular symptom score
qRT-PCR: Quantitative real-time PCR
FCM: Flow cytometry
ECG: Electrocardiogram
AIT: Allergen-specific immunotherapy
SPT: Skin prick test
SOP: Standard operating procedure
PI: Principal investigator
ITT: Intention-to-treat
INCs: Intranasal corticosteroids.
